### Sample size

For the sample size calculation, we applied a mixed-model Analysis of Variance (ANOVA) procedure, with a power of 0.80, a two-sided alpha of *α*=0.025 (Bonferroni corrected for two primary outcome measures), a correlation between the repeated measurements of *r*=0.70 and three repeated linearly decreasing measurements. Bessell and colleagues^17^ reported effect sizes of *d*=0.83 for appearance and *d*=0.80 for anxiety in a study on Face IT. However, as we are not certain that we will obtain such a large effect, we will consider a medium effect of *d*=0.50. To detect a medium effect, 56 participants are needed in both groups. As dropout is typically high in eHealth interventions,^33 34^ we anticipated a dropout of 50%. Therefore, 224 participants are needed in total.

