## Abstract

**Introduction:**

This paper outlines the study protocol for the Dutch Young People (YP) Face IT Study. Adolescents with a visible difference (ie, disfigurement) often experience challenging social situations such as being stared at, receiving unwanted questions or being teased. As a consequence, some of these adolescents experience adverse psychosocial outcomes and appearance-related distress. To address this appearance-related distress, an online psychotherapeutic intervention, YP Face IT, has been developed. YP Face IT uses social interaction skills training and cognitive–behavioural therapy. The Dutch YP Face IT Study tests whether this intervention is effective in reducing social anxiety and improving body esteem.

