**Methods and analysis:**

Participants are adolescents aged 12–18 with a visible difference and experiencing appearance-related distress. In this two-armed randomised controlled trial, 224 adolescents will be randomised to care as usual or YP Face IT. Adolescents will complete questionnaires at baseline, at 13 weeks and at 25 weeks. Primary outcomes are differences in social anxiety and body esteem between YP Face IT and care as usual. Secondary outcomes are differences in aspects of self-worth, perceived stigmatisation, health-related quality of life, life engagement, appearance-related distress and depressive symptoms between the two groups.

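### The only multiplicity rule stated for the two primary outcomes is a Bonferroni split; Holm's step-down would keep the same error control and gain power for the second outcome at little cost

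*Protocol article*

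**What the plan says.** The abstract of the protocol article (Methods and analysis) names two primary outcomes: "Primary outcomes are differences in social anxiety and body esteem between YP Face IT and care as usual". The abstract's Introduction says that the study "tests whether this intervention is effective in reducing social anxiety and improving body esteem".

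The Sample size section opens "For the sample size calculation, we applied a mixed-model Analysis of Variance (ANOVA) procedure". It then lists the inputs: power 0.80, a two-sided alpha of 0.025 explained as "Bonferroni corrected for two primary outcome measures", and "a correlation between the repeated measurements of *r*=0.70 and three repeated linearly decreasing measurements". On the effect it says "we will consider a medium effect of *d*=0.50". The result is 56 evaluable participants per group, and 224 in total after allowing for 50% dropout.

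The Statistical analysis section describes one multilevel model for each outcome. It gives no significance level for the final tests and no multiplicity procedure.

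**The concern.** If the planning alpha is carried into the analysis, each primary outcome must reach p ≤ 0.025 whatever the other one shows. Holm's procedure tests the smaller p-value at 0.025 and, only if that is significant, the other at 0.05. It needs no assumption about dependence to hold the familywise error at 0.05, and it can never reject less than Bonferroni.

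The stated aim covers both outcomes, and the planned 80% power applies to each one singly. The chance of showing both is therefore below 80%, and part of that shortfall comes from the choice of procedure and could be recovered without extra participants.

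**Working it through.** **Inputs from the Sample size section.** Two-sided alpha 0.025 per outcome, power 0.80, d = 0.50, r = 0.70, three measurements with a linear pattern, 56 per group, 50% dropout. The correlation between the two primary outcomes is not given; 0 to 0.7 is assumed below, with 0.9 as an extreme.

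**1. The plan's own figure.** Take a group-by-time F test with compound symmetry and group differences of 0, 0.25 and 0.50 SD over the three time points. The squared deviations from their mean sum to 0.25² + 0 + 0.25² = 0.125.

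- Noncentrality: λ = (n/2) × 0.125 / (1 − r) = 28 × 0.125 / 0.30 = 11.67, with 2 and 2 × (112 − 2) = 220 degrees of freedom.
- Power at alpha 0.025: 0.799. The stated 56 per group is reproduced (57 is the first n to reach 0.80 exactly).
- Total: 112 / (1 − 0.5) = 224, as stated.

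**2. Error control.** Bonferroni: 0.025 + 0.025 = 0.05 at most, or 1 − 0.975² = 0.0494 if the tests are independent. With both nulls true, Holm makes a false rejection in exactly the same cases as Bonferroni, because nothing is rejected unless the smaller p-value is ≤ 0.025. With one null true and the other effect at d = 0.50, simulation (200,000 runs, 56 per group, correlation 0 to 0.9) puts Holm's error on the true null at 0.043 to 0.045, against 0.025 under Bonferroni. That is still below 0.05.

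**3. Power when both effects are real.** Use normal test statistics with 80% power each at two-sided 0.025.

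- Mean of each statistic: 2.2414 + 0.8416 = 3.0830.
- Power at two-sided 0.05: Φ(3.0830 − 1.9600) = 0.8693.

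Write A for significance at 0.025 and A′ for significance at 0.05, with subscripts for the outcomes.

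- Both, Bonferroni: P(A₁ and A₂).
- Both, Holm: 2 × P(A₁ and A′₂) − P(A₁ and A₂).
- At least one, either method: 2 × 0.80 − P(A₁ and A₂).
- Per outcome, Holm: by symmetry, (at least one + both under Holm) / 2.

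For independent tests:

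- Both, Bonferroni: 0.80² = 0.640.
- Both, Holm: 2 × 0.80 × 0.8693 − 0.640 = 0.751.
- At least one: 1.60 − 0.640 = 0.960.
- Per outcome, Holm: (0.960 + 0.751) / 2 = 0.855.

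The same formulas with bivariate normal probabilities give:

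| Correlation (assumed) | Both, Bonferroni | Both, Holm | At least one, either method | Per outcome, Bonferroni | Per outcome, Holm |
|---|---|---|---|---|---|
| 0 | 64.0% | 75.1% | 96.0% | 80% | 85.5% |
| 0.3 | 66.6% | 76.6% | 93.4% | 80% | 85.0% |
| 0.5 | 68.7% | 77.8% | 91.3% | 80% | 84.6% |
| 0.7 | 71.3% | 79.4% | 88.7% | 80% | 84.1% |
| 0.9 | 75.0% | 81.5% | 85.0% | 80% | 83.2% |

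Simulating the F test at 56 per group agrees to within about half a percentage point (for example 63.9% against 75.2% at correlation 0, and 70.8% against 79.2% at 0.7).

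**4. Power when only one effect is real.** Holm helps the real effect only if the null outcome is falsely rejected first. For independent tests the gain is 0.025 × (0.8693 − 0.80) = 0.0017. Simulation gives 0.80 under both methods.

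**The case against.** The strongest reply is that the article nowhere says the final tests use plain Bonferroni. The 0.025 explains an input to the sample size calculation, and planning at 0.025 suits Holm just as well, since that is Holm's first step. The rule for the final tests may stand in an analysis plan that is not shown. This stands: a reader might infer that each outcome is fixed at 0.025 in the analysis. That is the natural reading of the only rule given, but it is not stated. The point is therefore not that a rule is missing. It is that the one rule stated has a uniformly more powerful alternative.

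Second, nothing in the plan is wrong on this point. The alpha is split correctly, the familywise error is controlled, and the sample size reproduces. This also stands. A reader might infer from the 64–71% that the trial is underpowered. The protocol does not support that: it sets its 80% per outcome and names no target for both together. Although the aim joins the two outcomes, the document does not say that success needs both. Splitting alpha implies that either outcome alone can carry a claim. If both were required, each could be tested at 0.05 with no split, giving 0.8693² = 75.6% for independent tests.

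Third, the gain is conditional. It arises only for the second rejection, when both effects are real. That stands, but both effects being real is a reasonable planning case: the section cites earlier effects of d = 0.83 for appearance and d = 0.80 for anxiety.

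Fourth, Holm is not free. Bonferroni's 97.5% intervals match its tests exactly. Under Holm, an outcome declared significant with p between 0.025 and 0.05 has a 97.5% interval that includes zero. That is a real, though small, cost.

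**Conclusion.** The point holds as an inexpensive improvement to a valid plan. Holm gives the same familywise guarantee of 0.05 and never rejects less than the Bonferroni split. If both effects are real, it adds about 4 to 6 percentage points of power per outcome and about 8 to 11 points for showing both, over an assumed correlation of 0 to 0.7. At 0.9 the gains are about 3 and 6 to 7 points. These figures rest on equal power of 80% per outcome at 0.025 and on the assumed correlation. Power for at least one outcome does not change, and power when only one effect exists changes by at most about 0.2 points. The planned 56 evaluable per group and 224 in total need no revision.

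**What to change.** Add one sentence to the Statistical analysis section, before unblinded analysis: the two primary outcomes are tested with Holm's procedure at an overall two-sided 0.05, the smaller p-value at 0.025 and, if that is significant, the other at 0.05. Leave alpha = 0.025 in the Sample size section and describe it there as Holm's first step. If an analysis plan already specifies a step-down test, the article only needs to say so.

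The change needs no extra participants, data or visits. If 97.5% intervals are reported, note beside them that they may include zero for a second outcome that Holm declares significant.

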### Statistical analysis

The data will be analysed using multilevel linear regression analyses. There will be two levels in the models. The participants constitute the upper level and their repeated measures the lower level. For each outcome variable, a model will be postulated using treatment group, time and interaction with treatment group as fixed effects. Time will be entered in two ways: categorical and continuous. First, for categorical, we will postulate a model with T2 (direct follow-up) and T3 (3-month follow-up) using T1 (baseline) as reference group. Second, for continuous, we will apply the logarithm of time, as generally treatments have the largest effect at start and the level of functioning stabilises on the long run. The deviance statistic using restricted maximum likelihood will be applied to determine the covariance structure. The deviance test will be used to determine whether the more parsimonious (log) model is a too rigorous oversimplification.^35^ Effect sizes will be calculated from dividing differences between the primary time point (ie, 3 months) estimations and baseline by the estimated baseline SD. Analyses are done on an intention-to-treat base.

Participants who do not experience subclinical symptoms at T1, and are thus not randomised, will not be included in the analyses.

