### Randomisation and blinding

Participants will be randomised to either the CAU or the YP Face IT group in a 1:1 ratio. Randomisation will be stratified by age (12–13, 14–15 or 16–17 years old). Randomisation will be done using a list with a random sequence, generated using a computer programme. With the stratification, six different types of blocks can be formed. Each block will independently vary between four and eight randomisation pairs. The adolescents are informed of the group they are randomised to through email. The researcher analysing the data will be blind to the randomisation and will not be involved in monitoring the adolescents in the intervention. This researcher also supervises data collection by students, who are not blinded. The participants, the clinical psychologist and students monitoring the adolescents in the intervention will not be blind to the treatment conditions. When contacting the research team, the adolescents are explicitly instructed not to talk about the group they were allocated to.

If, through monitoring, the research team suspects that a participant experiences clinically significant symptoms, unblinding may take place. The participant will be excluded from the study and will be transferred to more appropriate care.

Participants that drop out after randomisation will be asked if they are willing to complete the questionnaires at T2 and T3. They are in no way obliged to do so.

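### The outcome model estimates a baseline arm difference that randomisation already sets to zero; a common T1 mean would be a free gain in precision, about 8–9% of the effect-estimate variance under the planned dropout

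*Protocol article*

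**What the plan says.** The Statistical analysis section describes a two-level linear model, with repeated measures within participants, in which "a model will be postulated using treatment group, time and interaction with treatment group as fixed effects". Time enters in two ways. In the categorical version, "we will postulate a model with T2 (direct follow-up) and T3 (3-month follow-up) using T1 (baseline) as reference group"; in the other, "for continuous, we will apply the logarithm of time". The effect measure follows the same logic: "Effect sizes will be calculated from dividing differences between the primary time point (ie, 3 months) estimations and baseline by the estimated baseline SD". Analysis is by intention to treat.

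The Study design section has T1 completed first, then screening on the T1 scores, then randomisation. Under Randomisation and blinding, "Participants will be randomised to either the CAU or the YP Face IT group in a 1:1 ratio", stratified by three age bands. The Sample size section assumes "a correlation between the repeated measurements of *r*=0.70", d=0.50, two-sided alpha 0.025 and power 0.80. It arrives at 56 per arm, and doubles this for 50% dropout to 224 in total.

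**The concern.** With T1 as an outcome row and the reference level, the coefficient for treatment group is the arm difference at T1. The group×T3 coefficient is the difference between arms in change from T1 to T3. Because T1 precedes randomisation, the arms have the same expected T1 mean. A free parameter for that difference removes no bias, and its sampling error passes into the treatment effect.

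What is at stake is precision on both primary outcomes, and on the secondary ones, in a trial that expects to lose half its participants. The loss is larger if the true correlation is below the assumed 0.70.

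**Working it through.** **Inputs.** From the Sample size section: r=0.70, d=0.50, two-sided alpha 0.025 (critical value 2.2414), 56 per arm after dropout, 50% dropout, so 112 randomised per arm. Assumed here: equal variances (set to 1) and the same correlation between any two visits. The values d=0.40 and r=0.50 are sensitivity values, not the protocol's.

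**The plan's own figure.** Take a 2-df group×time F test with arm differences of 0, 0.25 and 0.50 SD. The sum of squares about the mean is 0.125, and the noncentrality at 56 per arm is (56/2)×0.125/(1−0.70) = 11.67. Power is 0.799, and 57 per arm gives 0.807. So 56 is essentially reproduced, with no baseline constraint. Doubling 112 for 50% dropout gives 224.

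**Complete data.** The variance of the T3 effect estimate is 2v/n, with n per arm.
- Free T1 difference: v = 2(1−r) = 0.60.
- Common T1 mean: v = 1−r² = 0.51.
- Saving: 1 − 0.51/0.60 = 15%, which equals (1−r)/2.

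**50% dropout, T1 scores kept.** Suppose all losses occur before T2, so each arm has 112 T1 scores and 56 completers. Scaled to n=56:
- Free T1 difference: v = (1−r²) + (1−r)²/2 = 0.51 + 0.045 = 0.555.
- Common T1 mean: v = 0.51.
- Saving: 1 − 0.51/0.555 = 8.1%.

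If half of the dropouts leave before T2 and half after it, generalised least squares gives variances of 0.01879 and 0.01718, a saving of about 8.6%.

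**Power for the T3 contrast, 56 completers per arm, losses before T2.** Power = Φ(d/√(2v/56) − 2.2414).

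| d | r | v free | v common | Power free | Power common |
|---|---|---|---|---|---|
| 0.50 | 0.70 | 0.555 | 0.51 | 90.5% | 92.8% |
| 0.40 | 0.70 | 0.555 | 0.51 | 72.6% | 76.5% |
| 0.50 | 0.50 | 0.875 | 0.75 | 72.1% | 79.2% |

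At r=0.50 the saving is 25% with complete data (1.00 to 0.75) and 1 − 0.75/0.875 = 14.3% with this dropout.

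**Log-time model.** The article does not give the coding. Assuming log(weeks+1), which is zero at T1, the saving in the estimated effect at 25 weeks at r=0.70 is 19.5% with complete data and 10.8% to 14.1% under the two dropout patterns.

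**Age stratum.** Suppose age explains a share R² of the outcome variance, constantly over time. With complete data the change-score variance is 2[(1−R²) − (0.70−R²)] = 0.60 for any R², so adding age to the model as written saves nothing. With a common T1 mean and R²=10% (an assumption), v = 0.90 − 0.60²/0.90 = 0.50 against 0.51, a further 2.0%. At R²=2% the further saving is 0.4%.

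**The case against.** The strongest reply is that nothing here is an error. Group, time and their interaction, with baseline as an outcome row, is a standard model and is unbiased under randomisation. It also matches the procedure used for sizing. All of that stands. A reader might infer that the trial is underpowered or its result biased; the documents do not support either, since 56 per arm is essentially reproduced without the constraint.

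A reader might also take 15% as the loss to expect. That figure needs complete data. The protocol plans for 50% dropout, and a multilevel model can use the T1 scores of those who leave, so the free-baseline model already recovers part of the loss. Setting the complete-data variance of 0.60 against 56 completers would suggest a power gain at d=0.50 from 88.0% to 92.8%. With T1 scores kept, the gain is about 2 points, not 5.

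Finally, a reader might blame the missing age term, on the ground that omitting a stratification factor inflates standard errors. For this model it does not: a time-constant age effect cancels from the T1-to-T3 contrast. Only an age effect on change would matter, and the documents give no sign of one. A condensed article may also leave covariates to a fuller plan, so its silence on age is not a finding. The free group main effect differs, because the article states it.

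**Conclusion.** A free improvement, on efficiency alone. The stated model spends a parameter on a difference known in advance to be zero. At r=0.70, removing it lowers the variance of the T3 treatment-effect estimate (not of the outcome) by 15% with complete data and by about 8–9% under the planned dropout. Any correlation below 1 gives some gain, and a lower one gives more.

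The figures rest on equal variances and correlations across visits, on T1 scores being kept for dropouts, and on dropout that the model handles without bias. The primary time point is given only as 3 months, which could mean T2 or T3. The complete-data 15% is the same for either, as is the 8.1% when all losses precede T2.

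**What to change.** In the categorical-time model, keep time, group×T2 and group×T3 and drop the group main effect, so that both arms share one T1 mean. Keep T1 as an outcome row so that participants with only baseline data still contribute. A model of T2 and T3 with the T1 score as covariate is not a substitute here, because those participants would leave it. In the log-time model, state the coding, make it zero at T1, and drop the group main effect there too. Apply this to all primary and secondary outcomes, and fix it before the analyst is unblinded.

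Optionally, add age stratum and age stratum×time as fixed effects, to follow the stratified randomisation; little precision should be expected from it.

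The cost is a changed model statement for each of the two time codings. Baseline scores and age are already collected, and the sample size need not change.

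### A deviance test on the trial's own outcomes decides whether the treatment effect comes from a log-time slope or from separate T2 and T3 contrasts; name the categorical contrast as primary in advance

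*Protocol article*

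**What the plan says.** The Statistical analysis section fits a multilevel model to each outcome, with group, time and their interaction as fixed effects. Time is entered in two ways. One is categorical, with T2 and T3 compared against T1. The other is continuous: "Second, for continuous, we will apply the logarithm of time, as generally treatments have the largest effect at start". The choice between them is stated as a rule: "The deviance test will be used to determine whether the more parsimonious (log) model is a too rigorous oversimplification". The section gives no level for this test and no coding for log time. It does not name one model or one contrast as confirmatory. Effect sizes are taken from model estimates at a primary time point glossed as 3 months.

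Study design places T2 at 13 weeks and T3 at 25 weeks. T3 is labelled the 3-month follow-up, but T2 is itself about three months after baseline.

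Sample size assumes "three repeated linearly decreasing measurements", with "a correlation between the repeated measurements of *r*=0.70" and "we will consider a medium effect of *d*=0.50", at a two-sided alpha of 0.025 for each of the two primary outcomes.

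**The concern.** The two models answer different questions. The categorical model estimates the group difference at T2 and at T3 separately. The log model estimates one slope per group and reads both visits off a fixed curve, so data at T2 help to determine the reported effect at T3.

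The log model is the one to be kept unless the deviance test rejects it. The trial's outcome data therefore decide what kind of treatment effect is reported for each Bonferroni-protected primary outcome. If the log curve is wrong and is kept, a fading effect looks more durable than it is and a growing effect is understated. An interval computed as though the model had been fixed in advance ignores the selection. Because the later follow-up exists to show whether the effect lasts, this is the question a fixed curve should not partly answer by assumption.

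**Working it through.** **Inputs from the article.** Alpha 0.025 two-sided per outcome, power 0.80, r = 0.70, d = 0.50, linear course, 56 per group, 50% dropout, 224 in total (Sample size); visits at weeks 0, 13 and 25 (Study design).

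**Assumptions.** Compound symmetry; SD = 1; d = 0.50 is the group difference in change reached at T3; deviance test by full maximum likelihood at 0.05; 56 per arm with complete data. Two codings of log time are shown because the article states none.

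**1. The plan's own figure.** For the 2-df group × time interaction with group differences (0, 0.25, 0.50):

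λ = (n/2) × Σ(δ − mean)² / (1 − r) = 28 × 0.125 / 0.30 = 11.67.

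With 2 and 220 degrees of freedom at 0.025, power at 56 per group is 0.799. The F-based requirement is 57 and the chi-square approximation gives 56, so the stated figure reproduces. 56/0.50 = 112 per group, or 224.

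**2. Ratio imposed by the log model.** The T2/T3 ratio is x₂/x₃.
- log(weeks+1): x = (0, 2.639, 3.258), ratio 0.81.
- log visit number: x = (0, 0.693, 1.099), ratio 0.63.
- A linear course by visit has ratio 0.50.

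**3. What the log model estimates.** Under compound symmetry the slope of the group difference is Σ(x − x̄)δ / Σ(x − x̄)².

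For log(weeks+1), x − x̄ = (−1.966, 0.673, 1.292), with sum of squares 5.988.
- Linear (0, 0.25, 0.50): 0.8145/5.988 = 0.1360. T2 = 0.36 (true 0.25), T3 = 0.44 (true 0.50, −11%).
- Fading (0, 0.50, 0.25): 0.6598/5.988 = 0.1102. T3 = 0.36 (true 0.25, +44%).

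For log visit number, x − x̄ = (−0.597, 0.096, 0.501), with sum of squares 0.617.
- Linear: slope 0.445. T2 = 0.31, T3 = 0.49 (−2%).
- Fading: slope 0.281. T3 = 0.31 (+23%).

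**4. How often the deviance test detects the misfit.** The categorical model has six mean parameters and the log model four, so the test has 2 df. Its noncentrality is n × (residual sum of squares from the log curve, summed over arms) / (1 − r). For log(weeks+1) with a flat control arm:
- Linear: residual 0.125 − 0.8145²/5.988 = 0.0142; λ = 56 × 0.0142/0.30 = 2.65; detected in 29% of trials.
- Fading: residual 0.125 − 0.6598²/5.988 = 0.0523; λ = 9.76; detected in 81%, missed in 19%.

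The result depends on the control arm's course. Over a range of plausible control courses, the linear effect's misfit is detected in about 17–48% of trials and the fading effect's misfit is missed in about 3–33%. Outside that range, controls that decline linearly by 0.3 or 0.5 SD by T3 raise detection for the linear effect to 70% or 91%. A 0.3 SD linear control decline raises the missed share for the fading effect to 45%.

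**5. Error rate and coverage of the two-step rule** (simulation, known variance, nominal 0.025):
- Type I error is about 0.035 (0.032 to 0.036) if the categorical branch uses its 2-df test.
- Type I error is 0.025 to 0.027 if that branch uses the T3 contrast.
- Coverage of the T3 interval after selection is about 0.96 to 0.975 against 0.975. The lowest value found was 0.953, for a fading effect with controls declining linearly by 0.3 SD.
- In fading-effect trials where log(weeks+1) is kept, coverage is about 0.925.

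**6. Precision given up by always using the categorical T3 contrast.** Variances are in units of 2/n.
- Categorical: 2(1 − r) = 0.600.
- log(weeks+1): 0.30 × 3.258²/5.988 = 0.532; SE ratio √(0.600/0.532) = 1.06.
- log visit number: 0.30 × 1.099²/0.617 = 0.587; SE ratio √(0.600/0.587) = 1.01.

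**The case against.** The strongest defence is that the log model is nested in the categorical one. The deviance test is therefore a legitimate lack-of-fit test announced in advance, and choosing a simpler model this way is accepted practice. The selection costs little: if the categorical branch uses the T3 contrast, type I error is essentially nominal. The larger biases belong to log(weeks+1); with log visit number they are much smaller. The 56 per arm is also the number expected after 50% dropout, and a multilevel model can use partial data from the rest of the 224, so the real test may detect misfit more often. All of this stands, and it limits the size of the point. It does not tell the reader which contrast is confirmatory, nor free the T3 estimate from the curve's assumption when the log model is kept.

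Three stronger readings may suggest themselves, and the article supports none of them.
- **That REML deviances are used to compare models with different fixed effects.** REML is mentioned only for choosing the covariance structure. The sentence on log versus categorical time does not say which likelihood is used.
- **That log time is undefined at baseline or depends on the unit.** This holds only for particular codings. Visit numbers 1, 2, 3 give log(1) = 0 at baseline and involve no unit. An article may leave the coding to the full plan.
- **That the linear planning course contradicts the analysis.** The categorical model contains a linear course, and 56 per group reproduces from that model's 2-df interaction. Under log courses reaching 0.50 SD at T3, the same test needs 48 to 56 per group, so the trial is not undersized on this account.

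**Conclusion.** The point holds in limited form. The stated rule lets the outcome data choose between a log-slope effect and separate visit contrasts. With two follow-up visits, the log option imposes the relation between the T2 and T3 effects. Under log(weeks+1) the T3 effect is understated by 11% if the true course is linear and overstated by 44% if it fades from 0.50 to 0.25 SD. Under log visit number the figures are 2% and 23%. At 56 per arm the deviance test often fails to catch the linear case under log(weeks+1), and catches the fading case more often than not with flat controls.

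Averaged over trials, the damage to error rate and coverage is modest. It is concentrated in those trials where a wrong log curve is kept. The sizes rest on compound symmetry, r = 0.70, d = 0.50 reached at T3, an assumed test level of 0.05, the coding of log time and the control arm's course, of which the article gives only the correlation and the size of d. The change is worth making because it is nearly free, not because the planned analysis is invalid.

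**What to change.** State that the primary analysis of each primary outcome is the categorical-time model, and that the confirmatory test is the group difference in change from baseline at one named visit, whatever the deviance test shows. Identify that visit as T2 or T3, since the 3-month gloss on the primary time point could fit either. Keep log time as a secondary description of the course, with its coding stated (visit number, or weeks with a given offset). If the deviance comparison is reported, give its level and say that it uses full maximum likelihood.

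The cost is a change of wording before the data are analysed. If the log shape is exactly right, the T3 contrast has a standard error about 1% (log visit number) to 6% (log(weeks+1)) larger than the log-model estimate. No change to the sample size follows from this point.

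### The covariance structure is left to a deviance test on the trial data. With three visits, fixing an unstructured matrix would be a cheap safeguard for the 0.025 level.

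*Protocol article*

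**What the plan says.** The Statistical analysis section of the protocol article plans a two-level linear model with group, time and their interaction, and measurements at T1 (baseline), T2 (13 weeks) and T3 (25 weeks). On the covariance it says: "The deviance statistic using restricted maximum likelihood will be applied to determine the covariance structure". It names no candidate structures, no test level and no default. The same section calculates effect sizes from the change between baseline and the 3-month time point.

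The Sample size section sets "a two-sided alpha of *α*=0.025 (Bonferroni corrected for two primary outcome measures"), "with a power of 0.80" and "a correlation between the repeated measurements of *r*=0.70 and three repeated linearly decreasing measurements". It states that "we will consider a medium effect of *d*=0.50", that "56 participants are needed in both groups", that "we anticipated a dropout of 50"%, and that "224 participants are needed in total". The Randomisation and blinding section says that the analysing researcher is blind to allocation.

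**The concern.** REML deviance is a proper tool for comparing covariance structures under one mean model. The difficulty comes afterwards, because a non-significant deviance test does not show that the simpler structure is true. If the correlation between T1 and T3 is somewhat lower than that between adjacent visits, an equal-correlation structure understates the variance of the T3–T1 change. When the departure is mild, the deviance test often misses it. The treatment test then uses a standard error that is too small, and part of the protection bought by the Bonferroni correction is lost. With three visits an unstructured matrix has only six parameters, so there is little to gain from running that risk.

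**Working it through.** **1. The plan's own figure.** Inputs from the Sample size section: d = 0.50, r = 0.70, three measurements with a linear trend, alpha 0.025, n = 56 per group. For the 2-df group-by-time F test under compound symmetry, λ = (n/2)·d²/[2(1−r)] = 28 × 0.25/0.60 = 11.67. With N = 112, the degrees of freedom are 2 and 2(N−2) = 220. Power is 0.799, so 56 per group is reproduced, and 112/(1−0.50) = 224. A 1-df test of T3–T1 change would need only 46 per group.

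**2. What happens if the simpler structure is wrongly kept.** Take equal SDs (set to 1), adjacent correlations of 0.70 and a T1–T3 correlation ρ13. Compound symmetry uses the mean correlation, (0.70 + 0.70 + ρ13)/3. For ρ13 = 0.60 that is 0.667. The assumed variance of the change is 2(1−0.667) = 0.667, and the true one is 2(1−0.60) = 0.80. The standard error is therefore too small by the factor √(0.667/0.80) = 0.913. The critical value 2.241 becomes in effect 2.241 × 0.913 = 2.046, a two-sided error of 0.041. The same arithmetic gives 0.033 for ρ13 = 0.65 and 0.048 for 0.55. These are bounds for keeping compound symmetry throughout, which the article does not propose.

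**3. The selection procedure.** Simulation without a treatment effect: compound symmetry (2 parameters) against unstructured (6 parameters) by a 4-df REML deviance test at 5%, then a two-sided 0.025 test of the T3–T1 group difference under the chosen structure. The candidates, the 5% level and ρ13 are assumptions. There were 200,000 trials per setting, complete data, 56 per arm, adjacent correlation 0.70. Ranges are over repeated independent runs.

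| ρ13 | Unstructured chosen | Error after selection | Fixed unstructured |
|---|---|---|---|
| 0.65 | 13% | 0.031–0.032 | about 0.025 |
| 0.60 | 39% | 0.032–0.034 | about 0.025 |
| 0.55 | 74% | 0.030 | about 0.025 |

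**4. Other settings under the same rule.**
- True compound symmetry, r = 0.70: 0.024–0.025.
- First-order autoregressive, r = 0.70 (ρ13 = 0.49), where unstructured is chosen in 96% of trials: 0.026–0.027.
- T1–T3 more highly correlated than adjacent visits: about 0.020.
- 112 complete cases per arm: at most about 0.031.
- 224 randomised with 50% dropout completely at random, adjacent correlation 0.73, ρ13 = 0.64: 0.0325 after selection and 0.023 with fixed unstructured (Monte Carlo standard error about 0.0025). The other covariance patterns tried with dropout gave 0.0225–0.026.
- A 20% selection level, 56 complete per arm, ρ13 = 0.65/0.60/0.55: 0.029/0.029/0.026.

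**5. The 2-df group-by-time test.** After the same selection at 5% with 56 per arm and ρ13 from 0.55 to 0.65, the error is about 0.026–0.027. With 112 per arm it is 0.025–0.026.

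**6. Cost of fixing unstructured.** With λ = 11.67 and degrees of freedom 2 and 109 instead of 2 and 220, power is 0.791 instead of 0.799.

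**The case against.** The strongest reply is that nothing here is stated wrongly. The rule is given in advance and uses the right likelihood for the purpose. It leaves an unstructured matrix open, and the blinded analyst cannot steer the choice towards a favourable result. All of that stands, although blinding does not repair a standard error that is too small.

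A second reply is that the size of the problem depends on candidates and a selection level that an article may leave to the full plan. This also stands, as the 20% level shows.

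A third is that the T3–T1 contrast appears in the article as the basis of the effect sizes. The article does not say that the 0.025 level applies to a 1-df test of it, and the stated 56 per group matches the 2-df test, where the inflation nearly vanishes. This is correct and limits the point considerably.

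A reader might infer that the primary analysis will exceed its 0.025 level, or that the error could reach 0.048. The documents support neither. The excess is conditional and can reverse, and the larger figure assumes that compound symmetry is always kept, whereas the deviance test moves away from it when the misfit is large.

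**Conclusion.** The point holds as a minor, optional improvement. Under the assumed comparison of compound symmetry with unstructured at 5%, and a mildly lower T1–T3 correlation (0.55–0.65 against 0.70), a 0.025 test of T3–T1 change can run at about 0.030–0.034 with 56 complete cases per arm. The excess is therefore about 0.005 to 0.009 per primary outcome. It is smaller with 112 per arm, small for the 2-df test, and essentially absent when compound symmetry is true or clearly wrong. Some decay of correlation over 25 weeks is plausible, but the article's single r = 0.70 does not establish it. A fixed unstructured matrix stayed close to 0.025 in every setting examined.

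**What to change.** Replace the deviance-based choice with a pre-specified unstructured covariance across T1, T2 and T3 for every outcome, with Kenward–Roger or Satterthwaite degrees of freedom. Name one simpler structure, to be used only if that model does not converge. The separate deviance test between categorical and logarithmic time is not touched by this change.

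The cost is one sentence in the analysis plan and about 0.8 percentage points of planned power (0.799 to 0.791 at 56 per group). The sample size need not change.
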